### Outcome measurements

The primary outcome will be the detection rate of fetal anomalies using first trimester 3D VR ultrasound in addition to the second trimester 2D ultrasound in a high risk population. Neonatal or histopathological examinations are considered the gold standard for the detection of congenital anomalies. For the detection rate analysis the sensitivity, specificity, positive and negative predictive values will be calculated for all ultrasound techniques for first trimester examination (i.e. 2D and 3D VR) in the intervention group and second trimester 2D examination in both groups (control group as well as intervention group). The detection rate of both first trimester examinations (i.e. 2D and 3D VR) will be compared. The detection rate of first trimester 2D will also be compared to the second trimester 2D ultrasound in the intervention group. In addition, we will assess the performance of the first trimester anomaly 2D and 3D VR ultrasound and the additional findings of the subsequent second trimester 2D ultrasound to gain a better insight into the whole diagnostic process.

The diagnostic performance of the first trimester ultrasound examination protocol will be compared to international ultrasound guidelines. Anatomical views (i.e. sagittal, transversal) according to our standardized protocol acquired per fetal structure will be evaluated as satisfactory or unsatisfactory. This assessment will be used to evaluate image quality per fetal structure and per modality, i.e. first trimester 2D and 3D VR. By doing this we will be able to examine the anatomical views which are essential to be included in the protocol, and the ones which are not. This evaluation will lead to optimization of the examination protocol in the future.

Secondary outcome measures will be health-related quality of life and cost-effectiveness of first trimester 3D VR ultrasound from a societal perspective. Health related quality of life will be expressed in physical, emotional and social functioning. Quality Adjusted Life Years (QALY’s) will be calculated from a maternal perspective, derived from the validated questionnaires. Actual expenses during the study will be measured using the standard costs as stated by the Dutch costing guidelines [37]. For each strategy (control versus intervention) the quality of life will be computed as well as the average costs per patient. The incremental cost-effectiveness ratio (ICER) will be calculated by dividing the difference in costs by the difference in quality of life. It represents the extra costs required to obtain one QALY. Furthermore, the cost per anomaly detected will be estimated. The cost-effectiveness analysis will span a period from approximately 8 weeks of gestation, when regular obstetric care starts, up to approximately 2 months beyond the estimated date of delivery. In this analysis, costs and effects will not be discounted due to a short time frame. Indirect costs will not be accounted for. The costs will be presented in Euros. The index year will be 2018.

Additionally, through a newly implemented questionnaire, the perspective of both patient and ultrasonographers on the new 3D VR modality will be surveyed. The participant perspective of the first trimester 3D VR ultrasound group (=intervention) will be compared to second trimester 2D ultrasound (=control).

An overview of all patients’ characteristics and data is shown in Table 1.

**Table 1 Tab1:** Patient characteristics collected within the VR FETUS study. Details of data collection form the first trimester up to 6 weeks after delivery are depicted

**Maternal Characteristics**	**Outcome**
Age	Years (mean ± SD)
Ethnicity	Dutch/Other western/Non-western
Level of education	Low, middle, high
Postal code	
Medical history	Unremarkable/Diabetes/Epilepsy/Other
Obstetrical history	Parity, miscarriage, previous pregnancy with congenital anomaly
Family history	Unremarkable/family members with congenital anomaly
Marital status	Married/not married
Global household income	€0–20.000/€20.000–35.000/€35.000–65.000/>€65.000 annually
BMI	Kg/m^2^ (mean ± SD)
Alcohol use during first trimester	No/Yes: how many units per day?
Smoking during first trimester	No/yes: how many cigarettes per day
Recreational drug use during first trimester	No/yes: what drugs; frequency per day?
Folic acid use during and/or prior to pregnancy	No/yes during pregnancy/yes started prior to pregnancy
Pregnant after artificial reproductive technology	No/yes: what type of assisted reproduction
First trimester screening for aneuploidy	No/yes: result
Medication	No/yes: what medication, dosage, starting and stopping date?
Antidepressant	Never/yes currently/yes previous use
**Questionnaires**	**Timing**
Current health status^a^	At inclusion, intervention or 13 weeks’ GA, 20 weeks’ GA, 6 weeks after due date
Anxiety and depression^b^	At inclusion, intervention or 13 weeks’ GA, 20 weeks’ GA, 6 weeks after due date
State and trait anxiety^c^	At inclusion, intervention or 13 weeks’ GA, 20 weeks’ GA, 6 weeks after due date
Current health status by VAS^d^	At inclusion, intervention or 13 weeks’ GA, 20 weeks’ GA, 6 weeks after due date
Medical consumption^e^	At 20 weeks’ GA, 32 weeks’ GA, 6 weeks after due date
Patient satisfaction with 3D VR	At intervention or 13 weeks’ GA, 6 weeks after due date
**Ultrasound**	**Measurements**
At inclusion, 1st trimester	Viability, CRL, multiple pregnancies, location
Intervention: 2D + 3D VR First Trimester Ultrasound, 1st trimester	Fetal anomaly scan using 2D and 3D VR. Growth parameters, detection of anomaly. See supplement A
Advanced fetal anomaly scan, 2nd trimester	Fetal anomaly scan using 2D. Growth parameters, detection of anomaly
**Pregnancy outcome**	**Outcome**
Outcome	Live birth, termination, intra-uterine fetal demise
Mode of delivery	Vaginal / Instrumental delivery / Cesarean section
Gestational age at delivery	Days (mean ± SD)
Invasive testing	No/yes: result
Date of invasive testing	
**Neonatal outcome**	**Outcome**
Birthweight	Birthweight, grams (mean ± SD)
Gender	Male/female
Congenital malformation	No/yes: what malformation
Prenatal diagnosis	Confirmed/discrepancy in findings: postnatal new or other findings

^a^SF-36: MOS 36-item Short Form Health Survey, ^b^HADS: Hospital Anxiety and Depression Scale, ^c^STAI: Spielberger State-Trait Anxiety Inventory, ^d^VAS: visual analogue scale, ^e^iMTA MCQ: iMTA Medical Consumption Questionnaire, CRL: Crown-Rump Length, 2D: two-dimensional, 3D VR: three-dimensional virtual reality

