### Study design (see Fig. 3)

The design is a randomized controlled trial amongst women with a high risk for fetal anomalies in their pregnancy. Participants will be allocated to either the control or intervention group. In the control group, participants will receive ‘care as usual’ according to the Dutch national guidelines. The intervention group will undergo an additional first trimester 2D and 3D VR ultrasound examination. Both groups will be asked to complete questionnaires on wellbeing, quality of life, stress, anxiety and medical costs.

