### Intervention group

The intervention consists of a first trimester 2D and 3D VR ultrasound examination between 11 and 14 weeks GA. The examination will be performed on a Voluson E10 (GE Healthcare, Austria) using a 4–9 MHz or 6–13 MHz high frequency transvaginal transducer or 2–6 MHz transabdominal transducer. A complete ultrasound examination will take 30–45 min per fetus. Ultrasound examinations will be performed according to international guidelines on safe use of ultrasound in the first trimester of pregnancy and as such, total scanning time will be kept as low as possible (ALARA-principle) [31].

The ultrasound examination will be performed by two examiners (examiner A and B) unable to see of each other’s results. Examiner A will perform the 2D ultrasound and (2D) evaluation of fetal organ structures using a protocol with standard anatomical views and measurements (Supplement 3). The cardiac examination, based on international ISUOG practice guidelines, is expanded with at least 7 measurements or planes: four chamber view with and without color Doppler, left outflow tract with color Doppler, right outflow tract with color Doppler, three vessel view, trachea view, tricuspid valve pulsed wave Doppler and a measurement of cardiac axis [32]. By default a transvaginal ultrasound examination will be performed. Only if fetal structures cannot be sufficiently visualized or if a women objects to a transvaginal examination, a transabdominal approach will be performed. During the 2D ultrasound examination, in addition to the already described 3D ultrasound datasets, four-dimensional spatio-temporal image correlation (4D STIC) datasets of the fetal heart will be acquired. Examiner B will evaluate the acquired 3D volumes using the 3D VR Desktop system [18]. Participants undergoing the first trimester scan will be unable to see the 2D scan. This is necessary to test their experience and objective reaction with respect to the 3D VR images. Thus, the influence of 3D VR ‘holograms’ on future parents’ perception can be investigated and compared to their 2D ultrasound experience later in pregnancy (at 20 weeks).

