The 3D VR images will be extensively discussed with the future parents: this will take 30 min. At the end of the 3D VR evaluation and discussion, examiners A and B will compare their findings to reach agreement. In case of an anomaly, participants will be informed about the presence or suspicion of malformations by examiner B. Routine care will then be offered, consisting of an advanced anomaly scan by an experienced and independent sonographer.

In the absence of an anomaly, the intervention group will undergo a routine second trimester 2D ultrasound scan as part of ‘care as usual’.

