### Statistical issues

#### Sample size

The prevalence of anomalies in the high risk group is 5–10% [38, 39]. The detection rate for fetal anomalies with 2D ultrasound in the first trimester lies between 18.2 and 71.8% [7]. As mentioned before, the detection rate in a high risk population is estimated at 61%, and in a low risk population at 63% for 2D ultrasonography [6, 8]. The detection rate for anomalies of the first trimester 3D VR ultrasound is 62.5% [20]. For second trimester (18–22 weeks’ gestation) 2D ultrasound the detection rate lies between 44.3 and 74.4% [40–42].

For sample size calculation with a superiority analysis we assumed a 65% detection rate for a second trimester 2D ultrasound examination and a 70% detection rate for the combined detection of first trimester 3D VR and second trimester 2D ultrasound examination in a high risk population. With an assumed prevalence of 7.5% and an alpha-error of 0.05 with a desired power of 0.80, a total group of *N* = 2800 is required.

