Some challenges remain. The introduction of a first trimester ultrasound examination will necessitate an additional prenatal visit, as well as expertise and training of staff. This might increase healthcare costs. This study will add new understanding on maternal psychological functioning throughout pregnancy in relation to prenatal ultrasound. Ideally, we would use structured interviews. However, due to the size of the study this was not a possibility. Instead we chose to use validated questionnaires to investigate maternal stress and anxiety.

Some organ systems are not yet fully developed in the first trimester or are too small to be visualized in detail. As an example, one can state that it is not possible to detect all or a large proportion of fetal cardiac and brain anomalies in early pregnancy. Therefore, second trimester ultrasound examination cannot be omitted, and has to be used in addition to first trimester ultrasound.

From a clinician’s point of view, the first trimester ultrasound should be studied regarding its additional value of diagnostic performance. Rather than comparing first and second trimester ultrasound examination, the performance should be based on the combination of first and second trimester. We expect that first trimester detection will show an improvement in the clinical care of participants and lead to significant improvement in their quality of life. Furthermore, a second trimester ultrasound examination will show the development of a congenital anomaly over time. Parents’ decision for continuation of the pregnancy is likely to be affected by this. The second trimester ultrasound is indispensable, therefore we will study the combined first and second trimester ultrasound examination compared to the second trimester only.

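### The primary outcome names first-trimester 3D VR plus second-trimester 2D, while the intervention arm delivers and acts on an agreed first-trimester 2D and 3D VR result

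*Protocol article*

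**What the plan says.** Outcome measurements in the protocol article defines the primary outcome: "The primary outcome will be the detection rate of fetal anomalies using first trimester 3D VR ultrasound in addition to the second trimester 2D ultrasound". Sample size assumes 65% detection for second-trimester 2D and "a 70% detection rate for the combined detection of first trimester 3D VR and second trimester 2D ultrasound examination". The Abstract (Methods) and Primary study objective also name 3D VR and second-trimester 2D. First-trimester 2D is not part of the primary combination in any of these places.

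The strategy delivered is wider. Study design says: "The intervention group will undergo an additional first trimester 2D and 3D VR ultrasound examination". Under Intervention group, examiner A evaluates the 2D scan and examiner B the 3D VR volumes, each without the other's result. Then "examiners A and B will compare their findings to reach agreement", and it is after this step that parents are told of an anomaly.

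Two pathways follow. After a finding: "Routine care will then be offered, consisting of an advanced anomaly scan by an experienced and independent sonographer", with no timing given. Otherwise: "In the absence of an anomaly, the intervention group will undergo a routine second trimester 2D ultrasound scan".

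The Discussion describes the comparison as "we will study the combined first and second trimester ultrasound examination compared to the second trimester only", which is not limited to 3D VR.

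**The concern.** The trial randomises women between two strategies, so the primary numerator in the intervention arm should be what that strategy detects. The stated combination leaves out one of its two first-trimester readings.

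Suppose the 2D examiner sees an anomaly, the 3D VR examiner does not, the two agree that it is present, the parents are told, and the pregnancy ends before 18 weeks. The strategy has found the anomaly. On the literal outcome it is a miss, because 3D VR was negative and no second-trimester scan took place. The article expects such pregnancies: early termination is part of its rationale in Background, termination is a recorded outcome in Table 1, and Questionnaires provides adapted forms for it.

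The control arm has no first-trimester anomaly scan whose result could be discarded in this way. The loss would therefore fall on one arm and understate the effect. The trial is also unblinded and yields three first-trimester results per fetus (2D, 3D VR, agreed), so a numerator left open could be settled after the results are known.

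**Working it through.** **1. What is settled by reading.** Could 3D VR simply mean the whole first-trimester visit in the primary outcome? Outcome measurements itself treats 2D and 3D VR as separate techniques, plans to compare their detection rates, and lists 2D plus 3D VR followed by second-trimester findings only as a further assessment. Sample size quotes 61% for first-trimester 2D (high-risk population) and 62.5% for 3D VR, then puts only 3D VR into the powered contrast. The literal reading is therefore a real one, and it conflicts with the agreement step and with the Discussion.

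**2. The plan's own figure.** For 65% against 70%, two-sided alpha 0.05, power 0.80, 1:1 (sidedness and ratio are my assumptions):

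n = [1.960·√(2·0.675·0.325) + 0.842·√(0.65·0.35 + 0.70·0.30)]² / 0.05² = 1377 affected fetuses per arm, 2754 in total.

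The stated 2800 is close to that count. With the stated 7.5% prevalence applied, the requirement would be 2754 / 0.075 = 36,720 women, so 2800 women is not reproduced. That is a separate problem. The percentages below do not depend on N; only the fetus counts do.

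**3. Affected fetuses per arm.** 2800 × 0.075 / 2 = 105, taking one fetus per woman. The planned 5 points equal 0.05 × 105 = 5.25 fetuses.

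**4. Affected fetuses positive on first-trimester 2D only.** With p₁ = 0.61 (2D), p₂ = 0.625 (3D VR) and an assumed correlation φ between the readings:

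- joint = p₁p₂ + φ·√(p₁(1−p₁)p₂(1−p₂)) = 0.381 + 0.236φ
- 2D only = 0.61 − joint
- either reading positive = 0.625 + 2D only

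| φ (assumed) | Joint | 2D only | Of 105 | Either reading |
|---|---|---|---|---|
| 0.9 | 0.594 | 1.6% | 1.7 | 64.1% |
| 0.7 | 0.547 | 6.3% | 6.7 | 68.8% |
| 0.5 | 0.499 | 11.1% | 11.6 | 73.6% |
| 0 | 0.381 | 22.9% | 24.0 | 85.4% |

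**5. What is lost.** Let s be the share of 2D-only cases not found at a counted second-trimester scan. The understatement is s × (2D only). The documents give no value for s. Over φ from 0.9 to 0.5, it is 1.6 to 11.1 points if all are lost, 0.8 to 5.5 points if half are lost (an illustration only), and nil if the later scan recovers every case.

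**6. Which end is plausible.** Examiner B reads volumes acquired in examiner A's session, using the same protocol of views, and structures too small to see at that age would be missed by both. Correlation should be high. At φ = 0.5 the two readings together already detect 73.6%, above both the highest first-trimester 2D figure quoted (71.8%) and the 70% assumed for 3D VR plus second-trimester 2D. Independence gives 85.4%. The lower end of the range is the more credible.

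**The case against.** The best defence is that the article uses 3D VR ultrasound loosely. In Questionnaires it names the visit, in the secondary outcomes it names the intervention group, and Primary study objective speaks of an anomaly scan that uses 3D VR. Read with the Discussion, the sensible numerator was probably intended. No section sets out a per-fetus scoring rule, and such detail may stand in a fuller document. This defence has weight: the fault is an inconsistency, not a wrong rule firmly laid down. It does not dispose of the point, because the section that defines the primary outcome is the one that separates the two modalities.

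A reader might infer more than the documents support:

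- **That every 2D-only finding is scored as a miss.** It is not. Second-trimester 2D is in the same numerator and can recover the case.
- **That fetuses sent for the advanced scan after a positive finding are lost.** The timing of that scan is not given. Control group uses the same term for the 18–22 week examination, and Table 1 places the advanced scan in the second trimester, so it may be the counted scan.
- **That a 3D VR positive withdrawn at agreement would count as a hit.** The article does not say whether the pre-agreement or the agreed reading is scored.
- **That the bias could reach 11.4 points.** That is 22.9% × 0.5. It needs independent readings of one session and an unsourced loss of half the cases.

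**Conclusion.** The point holds as an inconsistency in the primary outcome with a foreseeable consequence in one arm. Taken literally, Outcome measurements and Sample size discard a detection made by first-trimester 2D, agreed and disclosed, when no counted second-trimester scan finds it. A pregnancy ending before 18–22 weeks is the clear example. The direction is then against the intervention.

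The size is uncertain. 2D-only positives range from 1.6% (1.7 fetuses) to 11.1% (11.6 fetuses) of affected fetuses for assumed correlations of 0.9 and 0.5. Only an unknown part of them is lost, and the lower end is more likely. This rests on 61% and 62.5%, which come from different cited sources, on 1:1 allocation, and on 105 affected fetuses per arm. Against a planned difference of about 5 fetuses, even one or two reclassified cases count, but the documents do not show that the planned effect would be wiped out.

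Severity: should-fix.

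**What to change.** - Define detection in the intervention arm once: an anomaly in the agreed first-trimester result (2D, 3D VR or both) or at the second-trimester scan. Compare it with detection at the second-trimester scan in the control arm.
- Use this wording in the Abstract, Primary study objective, Outcome measurements and Sample size, so that they match the Discussion. State that the 70% assumption refers to this combination, or revise it.
- Say whether the advanced scan offered after a first-trimester finding counts as the second-trimester scan for scoring.
- Keep the separate pre-agreement 2D and 3D VR readings for the comparison of modalities within the arm.

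The cost is wording only. The procedure already produces the 2D, 3D VR and agreed results. Each must be kept as its own data item, and the definition should be fixed before outcome data are examined.

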### Control group

In the control group, participants will receive ‘care as usual’ which consists of a viability and pregnancy dating ultrasound examination around 10 weeks’ gestation followed by counseling for aneuploidy testing. Aneuploidy testing will be performed either via the first trimester combined test or via non-invasive prenatal testing (NIPT). Furthermore, an advanced ultrasound examination between 18 and 22 weeks’ gestation will be performed to screen for fetal anomalies. When indicated, additional ultrasound examinations will be planned, for instance fetal cardiac evaluation with a pediatric cardiologist.

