### Questionnaires

All participants will fill out questionnaires on health related quality of life. The following validated questionnaires will be sent at fixed time points in pregnancy: the MOS 36-item Short Form Health Survey (SF-36), the Hospital Anxiety and Depression Scale (HADS), the Spielberger State-Trait Anxiety Inventory (STAI) and a visual analogue scale (VAS) for wellbeing [33–35]. The four questionnaires will be sent digitally to the participants on the day of inclusion, the first trimester 3D VR ultrasound (or after 13 weeks GA for the control group), the second trimester 2D ultrasound and 4 weeks after the estimated due date, respectively. The answers will be recorded on a secure webserver on the Erasmus MC premises.

Direct healthcare costs will be recorded using the iMTA Medical Consumption Questionnaire (iMTA MCQ) [36]. All significant costs and health effects on the short term up to 4–6 weeks after delivery or termination of pregnancy will be considered. Therefore, these questionnaires will be sent at 20 and 32 weeks GA and 4 weeks after the estimated due date. In case of an intra-uterine fetal demise or termination of pregnancy during the trial, women will be sent specifically adjusted questionnaires.

Participant perspective on the 3D VR ultrasound will be evaluated with an in-house developed questionnaire. This survey includes questions about the value of ultrasound imaging in the first trimester and personal perception of the added value of 3D VR. This questionnaire will be sent after the first trimester 3D VR ultrasound or around 13 weeks GA in the control group. This questionnaire will be validated in a subset of 50 participants.

Ultrasonographer opinion of both the first trimester 2D and the 3D VR ultrasound will be evaluated by another in-house developed questionnaire. More specifically, the additional value of the 3D VR in terms of patient understanding, counseling and detection of anomalies will be examined.

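### The participant survey is not scheduled at the second-trimester scan, so its timing does not support the stated comparison of 3D VR with second-trimester 2D ultrasound

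*Protocol article*

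**What the plan says.** The protocol article announces two comparisons of how participants perceive the scans.

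- **Between arms** (Outcome measurements): "The participant perspective of the first trimester 3D VR ultrasound group (=intervention) will be compared to second trimester 2D ultrasound (=control".
- **Within the intervention arm** (Intervention group): women do not see their first-trimester 2D scan, so that their perception of the 3D VR images can be studied and "compared to their 2D ultrasound experience later in pregnancy (at 20 weeks" weeks' gestation or thereabouts.

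The instrument is an in-house survey described under Questionnaires. It includes "questions about the value of ultrasound imaging in the first trimester and personal perception of the added value of 3D VR". On timing, that section says: "This questionnaire will be sent after the first trimester 3D VR ultrasound or around 13 weeks GA in the control group".

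Table 1 lists an item called "Patient satisfaction with 3D VR" with the timing "At intervention or 13 weeks’ GA, 6 weeks after due date".

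The scan that controls are meant to rate comes later. Under Control group, "an advanced ultrasound examination between 18 and 22 weeks’ gestation will be performed to screen for fetal anomalies".

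**The concern.** Comparing views of two scans requires an answer given after each of them, in terms that refer to it. For 3D VR the plan has this, because the survey follows the examination. For second-trimester 2D ultrasound it has no counterpart near the scan. The control form at about 13 weeks is completed before the scan that it would have to represent.

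Participant perspective is a declared objective of the trial. If the schedule is followed as written, analysts will have to use control answers given before the scan or answers recalled months afterwards. A difference from the immediate 3D VR answers could then reflect timing, recall or the outcome of the pregnancy as much as the imaging technique.

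**Working it through.** No sample size, power or error rate bears on this point. The check sets the survey schedule beside the scan schedule.

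**Inputs**

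- Control survey: about 13 weeks (Questionnaires; Table 1).
- Second-trimester scan: 18 to 22 weeks (Control group).
- Later survey: 6 weeks after the due date (Table 1 only).
- Due date: taken as 40 weeks. This is an assumption, as the article gives no figure.

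**Step 1: first control survey against the scan.** 18 − 13 = 5 weeks and 22 − 13 = 9 weeks. Controls answer about 5 to 9 weeks before the scan. Usual care has by then given them a viability and dating ultrasound and counselling on aneuploidy testing, but neither 3D VR nor the advanced 2D examination.

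**Step 2: the later survey against the scan.** The survey falls at 40 + 6 = 46 weeks. 46 − 22 = 24 weeks and 46 − 18 = 28 weeks. For a scan at 20 weeks the gap is 46 − 20 = 26 weeks. Delivery or the end of the pregnancy normally lies in between.

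**Step 3: what is collected near the scan.** In Table 1 the SF-36, HADS, STAI and VAS each have a 20-week time point, and so does the medical consumption questionnaire. The participant survey has none. The instruments sent at that visit measure health status, anxiety, depression, wellbeing and use of care. None is described as measuring a woman's view of the scan.

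**Step 4: does the described content reach the second-trimester scan?** The topics named under Questionnaires are first-trimester imaging and the added value of 3D VR, and the Table 1 label refers to 3D VR alone. Second-trimester 2D ultrasound is not named in either place. The form itself is not shown, so this is an indication and not proof.

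**Step 5: do the two schedules agree?** Questionnaires gives one sending of the survey and Table 1 gives two. The only administration after the second-trimester scan is the one on which they differ.

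**Result.** Neither the between-arm nor the within-woman contrast has a survey timed to the second-trimester scan.

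**The case against.** Four arguments can be made for the plan.

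**A post-delivery form exists.** Table 1 lists it without limiting it to one arm. By then controls with continuing pregnancies have had the second-trimester scan, and intervention women have normally had both. This stands as far as it goes. A reader might infer that the comparison is impossible, and the article does not support that: a weak retrospective version could be attempted.

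**The form is not shown.** The description says what the survey includes, which need not be everything, and the control and post-delivery versions may be worded differently. This also stands. A reader might infer that no participant will give any answer about the second-trimester scan, but that cannot be established from a condensed article. The timing, however, is stated outright and does not depend on the unseen wording.

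**The sentence may label arms and not scans.** On that reading the two bracketed terms describe the care each arm receives, and the 13-week control form is a gestation-matched comparator on the value of first-trimester imaging. This is possible and is a reason to keep that form. It does not settle the matter, because the section Intervention group names the 20-week 2D experience explicitly.

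**Hiding the 2D screen still has a use.** A reader might infer that the restriction on intervention women serves no purpose. That does not follow. Its direct reason is an uninfluenced reaction to the 3D VR images, which the survey after that examination captures. Only the further comparison with the 20-week scan is left without matching data.

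**Conclusion.** The point holds in this form: the survey schedule does not support the participant-perspective comparison that the article states. The perspective survey is not scheduled at the second-trimester scan in either arm. Controls answer about 5 to 9 weeks before it. The only later form, given in Table 1 but not under Questionnaires, comes about 24 to 28 weeks after it, with pregnancy outcome known. The second interval rests on a 40-week due date.

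The direction and size of any bias cannot be derived from the document. The consequence is confined to a lesser objective, and the detection-rate, quality-of-life and cost analyses do not depend on it. It still merits correction, because the mismatch is plain and inexpensive to remove.

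**What to change.** 1. Add short perspective items, worded for the scan just undergone, to the electronic questionnaires already sent at the second-trimester scan, in both arms.
2. Use them for the two stated contrasts: intervention women after 3D VR against control women after the second-trimester scan, and the change within intervention women from 3D VR to their own 20-week 2D scan.
3. State the limits that remain. Technique stays confounded with gestational age, and women whose pregnancies end before 20 weeks drop out of the comparison.
4. Keep the 13-week control form as a gestation-matched view of first-trimester imaging, but do not treat it as a rating of the second-trimester scan.
5. If no 20-week items are added, restate the comparison as one of views at about 13 weeks, and amend Outcome measurements and Intervention group to match.
6. Reconcile Questionnaires with Table 1 on whether the survey is sent once or twice.

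The cost is a small amendment and slight extra respondent burden. The mailing at the second-trimester scan already exists.
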